### Standard post-cancer directed treatment care

3.8

Participants who are randomized to the intervention or control group will continue to receive standard post-cancer directed treatment care at the time of enrollment and during the study.

Of note, participants who are randomized to the control group will only receive standard post-cancer directed treatment care. At the end of the study, however, these participants will be offered an exercise consult along with physical activity recommendations, a set of resistance bands, and a Fitbit (Inspire 3).

### Outcome assessments

3.9

All participants (n = 20) enrolled to participate in this study will receive baseline assessments the same day they provided assent, and their parents or legal guardians provided written informed consent. Moreover, they will receive follow-up assessments on weeks 4, 8, 12 and 16, as described in Table 1.

**Table 1 tbl1:** Outcome assessments over 16 weeks.

	Baseline	Follow-up week 1	Follow-up week 2	Follow-up week 3	Follow-up week 4	Follow-up week 5	Follow-up week 6	Follow-up week 7	Follow-up week 8	Follow-up week 9	Follow-up week 10	Follow-up week 11	Follow-up week 12	Follow-up week 13	Follow-up week 14	Follow-up week 15	Follow-up week 16
**Demographic information**	**I/C**																
**Cancer and treatment information**	**I/C**																
**Chronic pain**	**I/C**								**I/C**								**I/C**
**Pain medications**	**I/C**								**I/C**								**I/C**
**Pain medications (from medical records)**	**I/C**				**I/C**				**I/C**				**I/C**				**I/C**
**Psychosocial outcomes**	**I/C**								**I/C**								**I/C**
**PA behavior**	**I/C**	**I**	**I**	**I**	**I**	**I**	**I**	**I**	**I**	**I**	**I**	**I**	**I**	**I**	**I**	**I**	**I/C**
**Physical function**	**I/C**																**I/C**
Isometric handgrip strength	**I/C**																**I/C**
Aerobic capacity	**I/C**																**I/C**
Physical functioning	**I/C**																**I/C**

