### Study design

3.1

This is a single-site pilot randomized controlled trial where participants will be randomized in a 1:1 ratio to the 16-week behavioral PA intervention coupled with standard post-cancer directed treatment care, or to the standard post-cancer directed treatment care.

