### Participant-reported psychosocial outcomes

3.15

All participants will answer psychosocial questions using the PROMIS pediatric questionnaires [42], including self-reported physical function mobility (8-item), anxiety (8-item), depressive symptoms (8-item), fatigue (8-item), peer relationships (8-item), pain interference (8-item), pain intensity (1-item), sleep disturbance (8-items), cognitive function (7-item) and social isolation (8-item). The PROMIS pediatric questionnaire has excellent psychometric properties with a Cronbach's alpha coefficient of α > 0.90 for child self‐report and parent proxy-report [43].

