### Statistical analysis

3.18

Sample size calculations were not required for this single-site, pilot randomized controlled trial. The sample size of 20 is justified due to the limited availability of participants with the specific eligibility criteria being investigated.

Acceptability will be assessed and expressed as a percentage as follows: (number of patients enrolled × 100/number of patients approached).

Feasibility will be assessed by the number of participants randomized to the behavioral PA intervention coupled with standard post-cancer directed treatment care who complete more than 50% of the intervention calculated and expressed as a percentage, as follows: (number of interventions completed × 100/number of interventions planned). To note, the planned interventions are the support calls and text messages, as follows: weekly support calls (weeks 1–4), biweekly support calls (weeks 6 and 8) and texts (weeks 5 and 7), monthly support calls (weeks 12 and 16) and texts (weeks 9, 10, 11, 13, 14, 15).

The effects of the behavioral PA activity intervention coupled with standard post-cancer directed treatment care on secondary outcomes (total self-reported pain score, cumulative dose of pain medications, functional and psychosocial outcomes) will be explored using Repeated Measures Analysis of Variance (RM-ANOVA). RM-ANOVA [49] will be used to analyze both within-group and between-group differences in intervention effects. Cohen's *d* effect sizes [50] will be reported to quantify the magnitude of differences over time and to interpret the practical significance of the findings.

Drop-out and missing data will be accounted for and reported. If the reason is an adverse event during the intervention, it will be reported as well. In case of dropouts or missing data, an intention-to-treat analysis will be performed.

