### Data and safety Monitoring

3.20

Safety data including adverse events or serious adverse events will be collected through the Pediatric Module of the Patient-Reported Outcomes version of the Common Terminology Criteria for Adverse Events (Ped-PRO-CTCAE). The Ped-PRO-CTCAE will be used to monitor adverse events in both groups at baseline, 4, 8, 12 and 16-week follow-ups. The NIH NCI Ped-PRO-CTCAE form Builder to build a study-specific custom form related to the behavioral PA intervention to provide a more specific scope of the safety of the intervention. The form has been developed in collaboration with and reviewed by pediatric oncologists. The recall period for the Ped-PRO-CTCAE is the past 7 days. The Ped-PRO-CTCAE responses are scored from 0 to 4. Adverse events reported during the study procedure that are different from those assessed at baseline will be reported to the responsible IRB.

The study will be monitored by the Data and Safety Monitoring Committee (DSMC) and will require a review every 6 months and an audit yearly.

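### Pain is rated after baseline only at weeks 8 and 16; a brief rating sent with the existing week 4 and 12 safety form would be a cheap gain for an exploratory outcome

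*Protocol article*

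**What the plan says.** Protocol article, section 3.9 (Outcome assessments), states that all 20 participants have a baseline assessment and that "they will receive follow-up assessments on weeks 4, 8, 12 and 16, as described in Table 1". In Table 1:

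- Chronic pain, self-reported pain medications and psychosocial outcomes are marked for both arms at baseline, week 8 and week 16.
- Pain medications from medical records are marked for both arms at baseline and weeks 4, 8, 12 and 16.
- Physical activity behavior is weekly in the intervention arm, but only at baseline and week 16 in controls.

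So at weeks 4 and 12 the only both-arm entry is a review of records. Section 3.20 (Data and safety Monitoring) adds a participant-completed form that Table 1 does not list: the Ped-PRO-CTCAE "will be used to monitor adverse events in both groups at baseline, 4, 8, 12 and 16-week follow-ups".

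The pain instrument is the PedsQL pediatric pain questionnaire (section 3.12). A single PROMIS pain intensity item is part of the psychosocial battery (section 3.15). Section 3.18 (Statistical analysis) treats pain and medication dose as secondary outcomes, to be explored by RM-ANOVA, and names no target time point. On size it says: "Sample size calculations were not required for this single-site, pilot randomized controlled trial".

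**The concern.** The number of participants is fixed at 20 because few patients are eligible, so repeated measurement is one of the few remaining ways to sharpen the estimate of the effect on pain. Both arms are already asked to fill in a form at weeks 4 and 12, yet no pain rating is taken then. If the effect is summarized as an average over follow-up, two readings give a less precise estimate than four. If a participant misses week 8 or week 16, there is less nearby information to draw on.

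A smaller matter concerns medication. Over-the-counter use is sought in the self-report questionnaire (section 3.13), whereas the chart review and prescription monitoring described in section 3.14 concern prescriptions. Under Table 1 the prescription data are refreshed every 4 weeks and the self-reported data every 8.

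**Working it through.** The article gives no precision or power figure, so there is nothing to reproduce.

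**Inputs from the article:** 20 participants, 10 per arm; m = 2 follow-ups for pain now (weeks 8, 16); m = 4 if weeks 4 and 12 are added.

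**Assumption, not in the article:** correlation r between any two pain readings in one person, 0.5 to 0.7, equal for all pairs; equal variance at each visit.

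**Formulas.** The variance of the between-arm difference in mean follow-up pain, in units of 2σ²/10, is:

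- Unadjusted mean of follow-ups: (1 + (m − 1)r)/m
- Change from baseline: (1 + (m − 1)r)/m + 1 − 2r
- Baseline-adjusted: (1 + (m − 1)r)/m − r²

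| Analysis | r | m = 2 | m = 4 | Variance cut | Equivalent n (20 × ratio) |
|---|---|---|---|---|---|
| Baseline-adjusted | 0.5 | 0.500 | 0.375 | 25.0% | 26.7 |
| Baseline-adjusted | 0.6 | 0.440 | 0.340 | 22.7% | 25.9 |
| Baseline-adjusted | 0.7 | 0.360 | 0.285 | 20.8% | 25.3 |
| Change score | 0.5 | 0.750 | 0.625 | 16.7% | 24.0 |
| Change score | 0.7 | 0.450 | 0.375 | 16.7% | 24.0 |
| Unadjusted | 0.5 | 0.750 | 0.625 | 16.7% | 24.0 |
| Unadjusted | 0.6 | 0.800 | 0.700 | 12.5% | 22.9 |
| Unadjusted | 0.7 | 0.850 | 0.775 | 8.8% | 21.9 |

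For change scores the cut does not depend on r: the two variances are 1.5(1 − r) and 1.25(1 − r), and 1 − 1.25/1.5 = 16.7%.

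**Wider range of r.** At r = 0.3 and r = 0.8 the baseline-adjusted cut is 31.2% and 19.2%. The unadjusted cut is 26.9% and 5.6%.

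**Correlation that decays with time.** With AR(1) correlation of 0.7, 0.8 and 0.9 per 4 weeks, the baseline-adjusted variance of the average goes from 0.612 to 0.481, 0.545 to 0.425 and 0.368 to 0.282. That is a cut of about 21% to 23%.

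**Week 16 alone, complete data.** The variance is the same with two or four follow-ups (for example 0.942 in both cases at 0.7 per 4 weeks). The gain is 0%.

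**Illustration.** With baseline adjustment, r = 0.5, 10 per arm and an assumed two-sided 5% level and 80% power, the normal approximation gives a detectable average difference of 2.80 × √(0.500 × 0.2) = 0.89 SD with two follow-ups and 2.80 × √(0.375 × 0.2) = 0.77 SD with four.

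**The case against.** A reader might infer that the text and Table 1 contradict each other. They do not. The sentence in section 3.9 defers to the table, the table has a both-arm entry at weeks 4 and 12, and nothing promises every outcome at every visit. The wording is loose, since participants do not themselves receive a record review, but there are not two rival schedules.

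A reader might also infer that staff following Table 1 would skip the safety forms. Section 3.20 states the weeks for that form explicitly, Table 1 is a table of outcome assessments, and section 3.19 provides for written operating procedures. The documents do not support that harm.

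Other objections carry weight:

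- **Instrument.** The gain applies only to a measure that is actually taken four times. Adding the single PROMIS item leaves the PedsQL pain score with two follow-ups.
- **Model.** The plan specifies RM-ANOVA and names no averaged target. The 21–25% needs baseline adjustment and an average over visits; other analyses gain less, and week 16 with complete data gains nothing.
- **Dilution.** Sessions start short and build up (section 3.7), so an average that includes week 4 may understate a growing effect.
- **Medication.** The recall window of the questionnaire is not given. Its week 8 and week 16 completions may cover the intervals, so it cannot be said that over-the-counter use is missed.
- **Burden.** The full medication questionnaire also asks about smoking, cannabis and several therapies. Support calls at weeks 4 and 12 reach only the intervention arm, so for controls the safety form is the only documented contact.
- **Status.** The primary aims are feasibility and acceptability, which this point does not touch.

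**Conclusion.** The point stands as an inexpensive design improvement, not as an error. Two further pain readings per person would reduce the variance of an average follow-up effect by about 21–25% with baseline adjustment, 17% for change scores and 9–17% for unadjusted means. These figures rest on assumed correlations of 0.5 to 0.7 and on the same measure being used at all four visits. For a week 16 comparison with complete data there is no gain in precision, and the benefit is protection against missed visits. The article gives no drop-out rate, so that protection cannot be sized.

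A reader might take the equivalent of 25 to 27 participants as the loss in the present plan. That is the favorable end: it presumes a baseline-adjusted average that the article does not specify, and it would not apply to the PedsQL score if only the PROMIS item were added.

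**What to change.** 1. Send a brief pain rating with the safety form at weeks 4 and 12 in both arms. The single PROMIS pain intensity item is already in use. If the gain is meant for the main pain score, use instead the intensity rating of the PedsQL pain questionnaire.
2. Optionally add only the over-the-counter medication questions, not the whole questionnaire.
3. Analyse each measure over its own follow-ups in a baseline-adjusted repeated-measures model that keeps participants with incomplete data, in place of plain RM-ANOVA. Classical RM-ANOVA uses only participants with every reading, so extra visits under it could lose people. Report the week 16 difference separately, so that any dilution from early weeks is visible.
4. As tidying only, add the safety form as a row in Table 1 and reword section 3.9 to say which assessments fall at which week.

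The cost is one rating, and at most a few medication questions, at two existing contacts, plus an edit to the table and the analysis text. The downsides are slight extra burden on participants and an average that includes weeks when the effect may still be building.

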### Participant-reported demographic information

3.10

All participants will self-report their date of birth and gender. They will also describe their racial background, their ethnicity and the highest grade of school they completed at the time of enrollment.

### Participant-reported cancer and treatment information

3.11

All participants will self-report their age at cancer diagnosis, the duration of their cancer treatment, the time since their treatment ended, their cancer diagnosis, and the treatment regimen they received. If necessary, this information may be extracted from medical records.

### Participant-reported chronic pain

3.12

All participants will self-report their pain levels using the PedsQL pediatric pain questionnaire which is a symptom-specific instrument for children (8–12 years of age), and adolescents (13–18 years of age) to assess pain in pediatric patients with chronic health conditions [37]. The parent-proxy report format will be used to assess the parent's perceptions of their child's pain.

### Patient-reported pain medications

3.13

All participants will self-report their pain medication usage using a questionnaire developed by the study team. This questionnaire will record usage of prescribed and over-the-counter medications and will gather information about the use of non-prescription pain medications (e.g., over the counter oral and topical pain medications). Additional questions related to smoking behavior and cannabis/cannabinoids use [[38], [39], [40]] will also be asked and self-reported by all participants. Questions related to therapy to manage their pain (massage therapy, physical therapy, occupational therapy, chiropractic care and behavioral therapy) will also be asked and self -reported by all participants.

### Patient-unreported pain medications

3.14

For all participants, three other strategies will be used to collect data related to pain medications, as follows.•Chart review to gather information on prescription pain medication usage through medication reconciliation data. Information will be collected about number of pain medications prescribed, total dosage and length of time prescribed. This review will be conducted by the principal investigator who is a pediatric oncologist.•The PDMP (Prescription Drug Monitoring Program) will be accessed to gather information on all filled prescriptions for controlled substances within the state of Pennsylvania. This review will be conducted by the principal investigator who is a pediatric oncologist.•Morphine equivalent dose (MED) will be calculated for each patient after looking at the total daily amount of each opioid the patient is taking. Using the standard conversion factors developed by the CDC, the Morphine milligram equivalent (MME) equates the many different opioids into a standard value that is based on morphine and its potency providing an easily interpretable metric to represent opioid use [41]. This calculation will be conducted by the principal investigator who is a pediatric oncologist.

### Participant-reported psychosocial outcomes

3.15

All participants will answer psychosocial questions using the PROMIS pediatric questionnaires [42], including self-reported physical function mobility (8-item), anxiety (8-item), depressive symptoms (8-item), fatigue (8-item), peer relationships (8-item), pain interference (8-item), pain intensity (1-item), sleep disturbance (8-items), cognitive function (7-item) and social isolation (8-item). The PROMIS pediatric questionnaire has excellent psychometric properties with a Cronbach's alpha coefficient of α > 0.90 for child self‐report and parent proxy-report [43].

### Participant-reported PA behavior

3.16

All participants will self-report their PA behavior using the original version of the Godin Leisure Time Exercise Questionnaire (GLTEQ) to assess participants' weekly frequencies of strenuous, moderate and light activities for at least 15 min during a typical 7-day period (a week) [44]. They will also be asked to self-report how often they engage in any regular activities long enough to work up a sweat [44]. The GLTEQ has been widely used in pediatric oncology [45]. All participants will also self-report their weekly PA behavior using a PA questionnaire developed by the study team in order to capture the number of days per week that they are physically active (frequency), the number of minutes they were usually physically active (time), the type of PA they did (type), and the intensity of PA they did (intensity). This questionnaire will also capture their motivation, capability, and opportunities to be more physically active the next week.

### Physical function assessments

3.17

Maximum voluntary isometric handgrip strength of the forearm muscles will be measured, two times, using a calibrated Jamar hydraulic hand dynamometer. This assessment is a valid and reliable measure that has been reported to be easy for children and adolescents to understand and achieve [46].

Aerobic capacity will be measured using a 6-min walk test (6 MW T) [47]. Participants will be instructed to walk as fast as possible in a hallway for 6 min. Participants' perceived exertion (OMNI scale [48]), heart rate, oxygen saturation, blood pressure, and the covered distance will be measured. An equation to predict cardiorespiratory fitness (_pred_VO2_peak_) will be used [47].

Physical functioning will be measured using two different tests. During the 30-s chair stand test, participants will be instructed to complete as many full sit-to-stands as possible within 30-s. During the “Timed Up and Go” test, participants will be instructed to rise from a chair, walk 3 m (10 feet) around an obstacle, and then walk back to the chair and sit down. These tests will be performed twice. Participants' perceived exertion (OMNI scale [48]) will be measured.

### Statistical analysis

3.18

Sample size calculations were not required for this single-site, pilot randomized controlled trial. The sample size of 20 is justified due to the limited availability of participants with the specific eligibility criteria being investigated.

Acceptability will be assessed and expressed as a percentage as follows: (number of patients enrolled × 100/number of patients approached).

Feasibility will be assessed by the number of participants randomized to the behavioral PA intervention coupled with standard post-cancer directed treatment care who complete more than 50% of the intervention calculated and expressed as a percentage, as follows: (number of interventions completed × 100/number of interventions planned). To note, the planned interventions are the support calls and text messages, as follows: weekly support calls (weeks 1–4), biweekly support calls (weeks 6 and 8) and texts (weeks 5 and 7), monthly support calls (weeks 12 and 16) and texts (weeks 9, 10, 11, 13, 14, 15).

The effects of the behavioral PA activity intervention coupled with standard post-cancer directed treatment care on secondary outcomes (total self-reported pain score, cumulative dose of pain medications, functional and psychosocial outcomes) will be explored using Repeated Measures Analysis of Variance (RM-ANOVA). RM-ANOVA [49] will be used to analyze both within-group and between-group differences in intervention effects. Cohen's *d* effect sizes [50] will be reported to quantify the magnitude of differences over time and to interpret the practical significance of the findings.

Drop-out and missing data will be accounted for and reported. If the reason is an adverse event during the intervention, it will be reported as well. In case of dropouts or missing data, an intention-to-treat analysis will be performed.

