**Conclusions:**

This study will demonstrate that behavioral supportive measures like physical activity may be a novel means to improve cancer related chronic pain in young survivors of childhood cancer and decrease medication usage for pain along with improvement in functional and psychosocial outcomes.

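### Within-arm change is counted among intervention effects for 16 or 17 unranked secondary outcomes, and three sections promise a demonstration of benefit that a 20-patient exploratory analysis cannot give

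*Protocol article*

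**What the plan says.** Section 3.18 groups the secondary outcomes as "total self-reported pain score, cumulative dose of pain medications, functional and psychosocial outcomes" and applies repeated measures ANOVA to all of them, with Cohen's d as the effect size. It calls this exploration, and then states that "RM-ANOVA [49] will be used to analyze both within-group and between-group differences in intervention effects". Section 2 likewise lists comparisons within each group and between groups as secondary objectives. No outcome or contrast is put first.

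Section 3.15 supplies ten psychosocial scores: "PROMIS pediatric questionnaires [42], including self-reported physical function mobility (8-item), anxiety (8-item), depressive symptoms (8-item), fatigue (8-item), peer relationships (8-item), pain interference (8-item") and "pain intensity (1-item), sleep disturbance (8-items), cognitive function (7-item) and social isolation (8-item"). Section 3.17 supplies the functional tests.

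On size, "Sample size calculations were not required for this single-site, pilot randomized controlled trial"; 20 participants are randomised 1:1. The primary objective is acceptability and feasibility.

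On conclusions, the Abstract says "This study will demonstrate that behavioral supportive measures like physical activity may be a novel means to improve cancer related chronic pain", and goes on to less medication and better functional and psychosocial outcomes. The last paragraph of the Introduction gives demonstration of these benefits as the purpose of the trial. Section 3.22 sees a strong opportunity to demonstrate them. Section 4 says that, at this stage, effectiveness can only be a hypothesis, and makes a fully powered efficacy trial depend on whether the results justify it.

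**The concern.** Two features of the text combine badly.

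First, within-group differences are placed beside between-group differences as differences in intervention effects. Randomisation protects only the between-arm contrast. Section 3.4.1 admits patients less than one year after therapy who report pain lasting three months or longer. Recovery after treatment and regression to the mean could both improve scores in either arm. A change from baseline in the intervention arm mixes these with any effect of the programme.

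Second, the article promises a demonstration of benefit on pain, medication, function and psychosocial health, but does not say which outcome or contrast would carry that statement. With 16 or 17 outcomes and both kinds of comparison available, a favourable result somewhere is not strong evidence. Because section 4 ties the next trial to these results, a within-arm improvement or an isolated small p-value could be taken as grounds for an efficacy trial.

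**Working it through.** The plan gives no power, significance level or error rate, so there is no stated figure to reproduce. The check counts the outcomes and then asks how often an inert programme would yield a favourable result.

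**Count of outcomes**

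- Self-reported pain score: 1 (3.18)
- Cumulative dose of pain medication: 1 (3.18)
- PROMIS scores: 6 + 4 = 10 (3.15)
- Handgrip, 6-minute walk, chair stand, Timed Up and Go: 4 (3.17)

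Total: 1 + 1 + 10 + 4 = 16. Predicted VO2peak makes 17, but it is calculated by an equation within the aerobic capacity assessment and is not a separate test. Parent-proxy pain and physical activity behaviour are collected but are not in the 3.18 list. Each outcome has three comparisons (between arms, within intervention, within control), which gives 16 × 3 = 48 or 17 × 3 = 51.

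**Assumptions, none of them in the document**

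Two-sided level 0.05; normal baseline-to-week-16 changes; 10 complete patients per arm; equal correlation between outcomes of 0 to 0.7; no effect of the programme. For an outcome measured twice, the group-by-time test in repeated measures ANOVA equals the t-test on change. For pain and PROMIS, which are also measured at week 8, this is a simplification.

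**Between arms, favouring the programme, independent outcomes**

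Each test has a 0.025 chance of a significant result in the favourable direction.

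- 16 outcomes: 1 − 0.975^16 = 0.333
- 17 outcomes: 1 − 0.975^17 = 0.350

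**Simulation, 100,000 trials per setting**

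- Between arms: t = (mean_I − mean_C) / √((s_I² + s_C²)/10), significant in favour if t > 2.101 (18 df).
- Within intervention: t = mean_I / (s_I/√10), significant in favour if t > 2.262 (9 df).

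Chance of at least one favourable result, given as 16 / 17 outcomes:

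| Correlation | Between arms only | Between arms or within intervention, no time trend | Same, both arms improve by 0.3 SD of change |
|---|---|---|---|
| 0 | 33% / 35% | 50% / 52% | 91% / 92% |
| 0.3 | 25% / 26% | 37% / 39% | 74% / 75% |
| 0.5 | 20% / 20% | 29% / 31% | 62% / 63% |
| 0.7 | 14% / 14% | 22% / 22% | 48% / 49% |

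The between-arm rates are unchanged, apart from simulation error, when both arms share the 0.3 SD improvement. The within-arm route is what responds to it. A single pre-named between-arm test has a 5% chance of a false positive, 2.5% in the favourable direction.

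**The statements side by side**

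| Place | Status given to efficacy |
|---|---|
| Abstract, Conclusions | will be demonstrated (that activity may help) |
| Introduction, last paragraph | demonstration is the purpose |
| 3.18 | exploration |
| 3.22 | strong opportunity to demonstrate |
| 4 | hypothesis only |

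**The case against.** The secondary analyses are labelled exploratory, feasibility and acceptability are primary, effect sizes are planned, and section 4 is cautious. The Abstract sentence is itself softened by *may*. The sentence on repeated measures ANOVA can be read as loosely naming the within-subject and between-subject factors of the model. No significance threshold or success rule for efficacy is stated, so any error rate presupposes a rule that the article does not contain.

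Much of this stands. A significance level, a hierarchy or a multiplicity rule may sit in an analysis plan that is not shown, and their absence from a condensed article about an exploratory pilot is not a fault. Naming a lead secondary outcome is partly a matter of preference.

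A reader might also infer that an inert programme would *probably* yield an apparent benefit. For 17 outcomes, the chance of any between-arm p < 0.05 is 58%, 50% and 40% at correlations of 0, 0.3 and 0.5; over all 51 comparisons it is 88%, 81% and 71%. But these figures are two-sided. They include results favouring control, and the second set includes changes inside the control arm. Neither kind can show benefit from the programme. Nor is *at least 17* safe as a count, because the seventeenth outcome is derived.

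What the objection does not remove is the published wording: within-group differences are presented under intervention effects, and three sections speak of demonstration where two others do not. An unseen analysis plan cannot reconcile those sections.

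**Conclusion.** The point holds as one of interpretation and internal consistency. Within-arm change should not carry a statement of intervention effect, and the trial as designed cannot demonstrate benefit on its secondary outcomes.

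On between-arm results alone, a false favourable finding somewhere among the 16 or 17 outcomes occurs in about 14% to 35% of trials. That is well above the 2.5% for one pre-named contrast, but it is not probable. If within-intervention change also counts, the range is about 22% to 52% without a time trend. A misleading benefit becomes likely over most of the range only if within-arm change counts and patients improve anyway: about 48% to 92% at 0.3 SD. Such improvement is plausible given the eligibility criteria, but the document gives no figure for it. The larger hazard is therefore reading within-arm change as benefit, more than the number of tests. All percentages rest on the assumed 5% level, the assumed correlations and the simplified tests.

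**What to change.** In section 3.18:

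- State that any statement of effect will rest on the between-arm contrast, reported as an estimate with a 95% confidence interval.
- Label within-arm changes as descriptive only, and carry this into the within-group objective in section 2.
- Preferably name one lead secondary contrast, for example the between-arm difference in self-reported PedsQL pain at week 16.
- State that no conclusion of benefit will rest on the other outcomes.

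Reword the Abstract conclusions, the last paragraph of the Introduction and section 3.22 to match section 4: the trial will estimate preliminary effects and inform a later efficacy trial.

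The cost is a few sentences. The authors give up the option of claiming benefit from isolated or within-arm p-values. No new data are needed, and the feasibility and acceptability aims are untouched.
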